## STUDY GOALS AND OBJECTIVES

The objective of this study is to evaluate safety and feasibility of controlled CSF ELD in reducing ICP burden and improving outcomes of select severe TBI patients.

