### Intervention

ELD placement will be performed bedside or in operating room if patient is undergoing surgery but not under radiographic guidance and connected to the LimiTorr™ drainage system (Integra Neurosciences), and zero-leveled at the level of the tragus. The LimiTorr™ provides volume-limited drainage and shuts off at a maximum drainage of 10 mL/hour, by always leaving 10 mL of fluid in the 20 mL shut-off-burotrol. The burotrol will be primed with 10 mL of sterile water or saline and will only be drained to a maximum mark of 10 mL on the burotrol—stickers will be placed on the burotrol to ensure adherence to protocol. However, should overdrainage occur in a rare instance, the ELD will be clamped for 1 hour.

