#### ELD Drainage Pressure

ELD in patients without high ICP will be set at 15 mm Hg and those with high ICP at 20 mm Hg, with a maximum of 10 mL/h drainage of CSF.

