#### ELD Drainage Volume

No more than 10 mL CSF will be drained within 1 hour in either intervention arms; this will be ensured by using the LimiTorr ELD system as described before.

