## OUTCOMES

### Primary Outcomes

Both “intention-to-treat” and “treated as per protocol” analyses will be performed. Incidence of critical neuroworsening events will be compared between each arm, and between both ELD groups and control arm. Univariate and multivariable analyses will be performed using baseline variables, hourly NPI change, and volume of CSF drained per day for outcomes, ie frequency of neuroworsening events and death. Multivariable analyses will use stated adverse outcomes as dependent variables, and age group, sex, baseline ELD safety score, and pupillary abnormality as independent variables. Logistic regression will be performed using those variables that have an association with outcome with a *P*-value of ≤.10.

For feasibility, a comparison between proportion of patients in each arm who underwent ELD as per protocol will be performed. Comparison between the 2 ELD groups will be performed. Interactions will be tested for in all analyses.

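### The drainage limit is hourly, but the only drainage exposure named for analysis is a daily volume, which cannot show whether the limit was kept and can be cut short by the event it is meant to explain

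*Protocol article*

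**What the plan says.** The stated objective is to "evaluate safety and feasibility of controlled CSF ELD in reducing ICP burden" (Study Goals and Objectives), so control of drainage is part of what is being tested.

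That control is expressed per hour wherever it appears:
- Intervention: "The LimiTorr™ provides volume-limited drainage and shuts off at a maximum drainage of 10 mL/hour".
- ELD Drainage Pressure: the same hourly maximum, repeated beside the pressure settings.
- ELD Drainage Volume: "No more than 10 mL CSF will be drained within 1 hour in either intervention arms".

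The last of these sections adds of the cap that "this will be ensured by using the LimiTorr ELD system as described before". The Intervention section, to which it refers back, allows that the cap may fail: "However, should overdrainage occur in a rare instance, the ELD will be clamped for 1 hour".

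Primary Outcomes, in the statistical part of the article, lists the drainage exposure as "volume of CSF drained per day for outcomes, ie frequency of neuroworsening events and death". The same sentence takes pupillary index change by the hour. That section also plans a per-protocol analysis beside intention-to-treat, and a comparison of the proportions who had ELD according to protocol. It defines neither. The outcome lists under Methodology do not name overdrainage.

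**The concern.** The time scale of the exposure does not match that of the hazard. Risks to Human Subjects places the greatest herniation risk soon after drainage starts, and the first two STOP criteria use a 1-hour window. A variable summed over a day averages away the feature that the cap is meant to control.

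There is a second problem. The STOP Criteria end drainage after an early herniation, and the Data Safety and Monitoring Board section pauses it when an unexpected serious event is suspected. Either lowers that day's volume because the event happened. A regression of events on same-day volume therefore partly has the outcome determining the exposure.

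At stake is a question the trial should be able to answer for the planned phase 2/3 study: how often the hourly limit was kept, and whether drainage just before an event was within it.

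**Working it through.** **The article's own figure.** A 20 mL chamber in which 10 mL always remains allows 20 − 10 = 10 mL per hour. This reproduces the stated cap and implies a daily ceiling of 24 × 10 = 240 mL.

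**Does daily volume identify a breach?** Let the breach hour be *v* mL, followed by the 1-hour clamp, with constant flow *b* mL/h in the other 22 hours. The day totals *v* + 22*b*, against 24*b* without a breach, a difference of *v* − 2*b*. The article gives no size for an overdrainage hour, so I assume *v* = 20, the nominal chamber volume.

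| Base flow *b* | Breach day (20 + 22*b*) | Compliant day (24*b*) | Difference |
|---|---|---|---|
| 5 mL/h | 130 mL | 120 mL | +10 mL |
| 10 mL/h | 240 mL | 240 mL | 0 |

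At *b* = 10 the two days are identical. Twelve repeats of a 20 mL hour and a clamp also give 12 × 20 = 240 mL, now with 12 breaches. Between patients with different base flows, a 130 mL day with a breach lies below a compliant day at 6 mL/h (24 × 6 = 144 mL).

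**Direction at equal base flow.** With *v* = 20 the difference is 20 − 2*b*, which is never negative for *b* up to 10. For smaller breaches it is negative only when *v* < 2*b*. The worst case, *v* just above 10 and *b* = 10, is about 10 − 20 = −10 mL. The signal is therefore small, and usually positive or nil.

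**Simulation.** 20,000 days were simulated per setting under assumed conditions: hourly base flow averaging 3, 5 or 8 mL and held at or below 10; breach hours of 10 to 20 mL, each followed by a clamped hour; breach chance 1% or 5% per hour.

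| Mean base flow | Breach chance per hour | Mean mL, breach / other days | Correlation of breach with daily volume |
|---|---|---|---|
| 3 | 1% | 81.9 / 72.0 | 0.48 |
| 3 | 5% | 86.7 / 72.0 | 0.56 |
| 5 | 1% | 124.4 / 118.3 | 0.22 |
| 5 | 5% | 126.9 / 118.2 | 0.32 |
| 8 | 1% | 172.0 / 171.0 | 0.04 |
| 8 | 5% | 172.8 / 170.9 | 0.07 |

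The correlation fades towards zero as flow nears the cap. Every simulated breach day totalled 240 mL or less, so a check against the daily ceiling would have flagged none. The simulation includes the clamp but not the stopping and pausing rules.

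**Effect of stopping.** Take assumed days counted from the start of drainage. With 20 mL in hour 1, a herniation and the drain discontinued, the total is 20 mL. An event-free day at 5 mL/h totals 120 mL. The event day is 1 − 20/120 = 83% lower. Without any breach, 5 mL in hour 1 and then discontinuation gives 5 mL against 120 mL. The shortfall in both cases comes from the event, not from safer drainage beforehand.

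**The case against.** The strongest reply is that the article has other routes to a breach. Feasibility includes the proportion who had ELD according to protocol, a per-protocol analysis is planned, and the Intervention section treats the marked chamber as a matter of protocol adherence. A breach would naturally count against both analyses. The medical monitor receives critical neuroworsening events, the DSMB looks for a discrete contributing factor, and Quality Assurance names a protocol adherence reviewer. The full case report form is not shown: Table 4 lists no drainage volume at all, not even the daily one that is to be analysed, so hourly volume may well be recorded. All of this stands. A reader might infer that the trial cannot say whether drainage was controlled, or could not attribute a herniation to overdrainage. The documents do not support either inference. The limits are narrower: the per-protocol definition is not tied to the cap, and DSMB review starts from events, so breaches without an event would not surface there.

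A reader might also infer that daily volume would rank an uncontrolled day as the safer one, for example by setting a 30 mL hour, a clamp and 22 hours at 5 mL (140 mL) against a day at the cap (240 mL), which is 42% lower. That deficit comes from comparing different base flows. At 5 mL/h throughout, the compliant day is 120 mL and the breach day is higher. A 30 mL hour also fits poorly with a 20 mL chamber, and the planned model assumes no direction for the volume effect.

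Finally, the article calls overdrainage rare, and 30 patients may yield few or no instances. That argues against a new primary endpoint, not against a count: no breaches over a stated number of drain-hours would itself support the claim of control.

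**Conclusion.** The point holds in a limited form. The hazard is defined by the hour, and the only named drainage exposure is by the day. Under the assumed 20 mL breach, a day that breaks the cap can total exactly the 240 mL of a compliant day. In the simulation the correlation of breach with daily volume ran from 0.04 to 0.56, so the usual consequence is insensitivity rather than reversal. The clearer bias comes from drainage ended or paused by the event, which lowers the total irrespective of what preceded it. The breach sizes, base flows and breach rates are assumptions; the hourly cap, the clamp, the stopping and pausing rules and the daily variable are the article's own. Separately, ELD Drainage Volume presents the cap as guaranteed while Intervention provides for its failure, and the two should be reconciled. The change is worth making because it is cheap and bears directly on the trial's objective; it does not undermine the primary outcomes.

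**What to change.** 1. In the statistical Primary Outcomes section, keep daily volume as a descriptive measure of cumulative drainage. As the exposure for neuroworsening, use lumbar volume in a fixed number of hours before the event, or the highest hourly volume before it. The fixed look-back is easier to compare with event-free time, because a running maximum grows with time on the drain.
2. As a supporting feasibility measure, by ELD arm and not as a new primary endpoint, report the number of patients with any hour above 10 mL and the number of such hours per 100 drain-hours.
3. State that per-protocol ELD includes keeping the hourly limit.
4. Reconcile the wording of ELD Drainage Volume with the overdrainage contingency in Intervention.

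The cost is one hourly data field if it is not already recorded, alongside neuromonitoring that is already hourly, and some handling of repeated measurements. With few or no breaches the results will be descriptive. No change to the drainage rule is proposed.

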### Randomization

The study will enroll 30 severe TBI patients who will undergo 2-stage randomization into usual treatment, usual treatment plus early ELD placement if ICP ≤ 20 mm Hg, or late ELD if ICP ≥ 20 mm Hg (Figure). The process of randomization will be centralized through a secure computerized site.

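### The logistic model for neuroworsening screens covariates at P≤.10 in 30 patients, tests interactions throughout, omits randomized arm and lists an ambiguous pupillary covariate

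*Protocol article*

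**What the plan says.** The Randomization section sets the sample size: "The study will enroll 30 severe TBI patients who will undergo 2-stage randomization into usual treatment", with the lumbar drainage groups defined as "usual treatment plus early ELD placement if ICP ≤ 20 mm Hg, or late ELD if ICP ≥ 20 mm Hg".

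The statistical text under Primary Outcomes first plans a direct comparison: "Incidence of critical neuroworsening events will be compared between each arm, and between both ELD groups and control arm". This is to be done by intention to treat and per protocol.

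It then adds regression and describes the variables twice. The general sentence reads: "Univariate and multivariable analyses will be performed using baseline variables, hourly NPI change, and volume of CSF drained per day for outcomes". The specific one reads: "Multivariable analyses will use stated adverse outcomes as dependent variables, and age group, sex, baseline ELD safety score, and pupillary abnormality as independent variables". The selection rule follows: "Logistic regression will be performed using those variables that have an association with outcome with a *P*-value of ≤.10". The section closes with: "Interactions will be tested for in all analyses".

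Two other places bear on this. The Inclusion Criteria admit only patients whose pupils are symmetric and react on both sides. Table 2 (Neuroworsening Events) counts a new fall in pupillary activity (item 2) and new asymmetry or bilateral mydriasis (item 3) as outcome events.

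**The concern.** The article fixes four things that do not fit together well at this sample size.

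- **Selection.** Choosing covariates by their P-value and then reporting ordinary intervals from the same 30 patients makes the error bars too narrow. Any covariate that survives has been picked because its estimate was large in this sample.
- **Event count.** Four covariates plus interactions are asked of a handful of events.
- **Arm.** A model without randomized arm cannot say whether any difference between arms persists after adjustment.
- **Pupils.** A covariate that eligibility holds nearly constant carries no information. One measured after baseline would be part of what it is meant to predict.

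The trial's stated purpose includes identifying the select patients in whom lumbar drainage is safe, and its results are meant to inform a phase 2/3 protocol. A covariate reported as an independent predictor of neuroworsening could therefore influence later patient selection on very weak evidence.

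**Working it through.** The article states no power, effect size or model-size calculation, so there is no figure to reproduce.

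**Inputs.** N = 30 (Randomization). Four listed covariates and the P≤.10 threshold (Primary Outcomes). From the registry analysis under Risks to Human Subjects: new pupillary asymmetry 22%, new motor deficit 18%, death at 2 weeks 22.4%. The composite neuroworsening rate is not given. I assume 22% (the larger of the two neuroworsening components with a rate) to 40% (22% + 18% with no overlap). I also show 50%, because that maximizes the smaller of the event and non-event counts.

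**1. Events per parameter.** Expected events = 30 × rate. The four covariates have six two-way interactions (4 × 3 / 2), giving 10 parameters.

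| Assumed rate | Events | Per listed covariate (÷ 4) | With all two-way interactions (÷ 10) |
|---|---|---|---|
| 22% | 6.6 | 1.65 | 0.66 |
| 40% | 12 | 3.0 | 1.2 |
| 50% | 15 | 3.75 | 1.5 |

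Above 50% the non-events become limiting, so 3.75 is the ceiling whatever the true rate. For the single outcomes: death gives 30 × 0.224 = 6.7 events and 1.68 per covariate; motor deficit gives 30 × 0.18 = 5.4 and 1.35.

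**2. False passes through the screen.** If the four candidates are unrelated to outcome, independent, and tested at their nominal size, P(at least one passes) = 1 − 0.9^4 = 0.34. With six candidates it is 1 − 0.9^6 = 0.47. A conservative small-sample test would pass somewhat fewer.

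**3. Coverage after selection.** Take a covariate with no effect that has passed at P≤.10. Its 95% interval misses the null whenever P≤.05. In large samples, with one covariate in the model, coverage given selection is 1 − 0.05/0.10 = 50%. A null simulation at n = 30, with assumed covariate distributions, gave about 60-64%. The exact value depends on the test used for screening. A likelihood-ratio screen gives a smaller shortfall than a Wald screen, but coverage stays well below 95%.

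**4. Arm.** The general sentence lists baseline variables, hourly change in the Neurological Pupillary Index (NPI) and daily CSF volume. The specific sentence lists age group, sex, ELD safety score and pupillary abnormality. Arm is in neither. CSF volume is not a substitute: it is measured after randomization, and drainage is stopped or paused after certain events (STOP Criteria; Data Safety and Monitoring Board), so the event can alter it. Adding arm as one more candidate would not help. With an assumed 10 control and 20 drainage patients, a doubling of risk from 22% to 44% reaches P≤.10 by Fisher's test only about 20% of the time, so a real effect would usually be screened out.

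**5. Pupillary abnormality.** Three readings are possible.

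- *At baseline, in the ordinary sense:* the inclusion criterion makes it essentially constant. A column of zeros adds nothing to the rank of the design matrix, and its coefficient cannot be estimated.
- *After baseline:* it overlaps Table 2 items 2 and 3, so it partly predicts itself.
- *NPI below 3 in a reactive pupil at baseline:* some variation could remain, but the text does not say this is meant.

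The ELD safety score does not share this problem. Eligibility restricts it to 5 to 8 (the Table 3 maximum is 2 + 2 + 2 + 2 = 8), but it still varies.

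**The case against.** Several points on the other side stand.

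**The randomized comparison is already planned.** Safety is defined as the frequency of events between arms, and the direct comparison comes before any regression. A reader might infer from the missing arm term that the primary safety question goes unanswered. The documents do not support that. Nor does the article say that the regression is meant to give an adjusted arm effect; it can be read as a predictor model. That reading weakens the point about arm but leaves the screen, the event count and the pupillary term as they are.

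**Outright failure of the model is not the main risk.** A reader might infer that the regression will often separate or diverge. Simulations that force all covariates in together do fail often: 8% to 29% of runs under one set of assumptions. But the article plans to fit only variables that pass the screen, and that smaller model was non-estimable in under 1% of null runs in one simulation and 1.8% to 3.3% in another. Likewise, near-total failure with interactions comes from entering every arm-by-covariate term in one model, whereas the article says only that interactions will be tested. Extreme arm odds ratios cannot be charged to a model without arm; even unadjusted, about 17%-18% of null runs at n = 30 fall outside 1/3 to 3.

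**The event range is an assumption.** It uses two of the five Table 2 items, so 40% is not an upper bound. The ceiling of 3.75 per covariate does not depend on it.

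**A fuller plan may define more.** The pupillary term may be defined there, and the fitting method belongs there. The screen and the interaction tests, however, are stated in the article, so they are not omitted detail.

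**Conclusion.** The concern holds in limited form. As written, the regression selects covariates on the data it then analyses, with 1.65 to 3 expected events per listed covariate (3.75 at best). It has about a 34% chance of admitting at least one unrelated covariate, and the intervals for those admitted cover far less often than stated. It gives no adjusted arm effect, and one of its four covariates is uninformative or circular on two of three readings.

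These sizes rest on an assumed composite rate, on independence of the candidates, and on assumed covariate distributions in the simulation. The selection problem itself does not depend on the exact values.

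The unadjusted comparison between arms is untouched, and the decision to move to phase 2/3 is tied to the incidence of serious adverse events, not to regression predictors. This should be fixed, but it is not a fault that undermines the trial.

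**What to change.** Change the wording of the analysis section as follows.

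- State that the unadjusted comparison between arms, already planned, is the primary safety analysis, reported as a risk difference with an exact or Newcombe 95% interval.
- Delete the P≤.10 screen.
- If an adjusted analysis is kept, prespecify one model: randomized arm forced in plus one baseline covariate (age or ELD safety score), fitted by Firth-penalized or exact logistic regression.
- Remove pupillary abnormality, or replace it with baseline NPI, defined as such.
- Label interaction tests and any predictor modelling exploratory.

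The cost is wording only, with no change to data collection or conduct. The downside is that fewer exploratory odds ratios will be reported.

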## SAFETY CONSIDERATIONS

### Risks to Human Subjects

Critical neuroworsening events related to ELD and CSF drainage are neurological worsening events such as decrease in GCS score, development of new motor deficit, or a cerebral herniation event, and rarely death (Table 2). Given the greatest risk of neuroworsening from herniation is soon after drainage is commenced, all patients will have neurological checks ie GCS score, ICP measurement, automated pupillometry for pupillary size, symmetry and NPI performed every 15 minutes for 1 hour after ELD placement, and start of CSF drainage. If NPI drops <3 within the first hour, a head CT may be obtained to review any craniocaudal shift. After the first hour, measurements will be performed hourly.

**TABLE 2. T2:** Neuroworsening Events

Critical neuroworsening events per SIBICC protocol
1. Spontaneous decrease in the GCS motor score of ≥1 points (compared to previous exam)
2. New decrease in pupillary activity
3. New pupillary asymmetry or bilateral mydriasis
4. New focal motor deficit
5. Herniation syndrome or Cushing Triad which requires an immediate physician response

GCS, Glasgow Coma Scale.

Based on inclusion/exclusion criteria, we analyzed the severe TBI BTF-New York State TBI-trac database from 1997 to 2007, with 1100 patients. The inclusion criteria applied to 47% of all severe TBI patients admitted over 10 years to 11 level 1 trauma centers in the state; 22% (95% CI: 19.9%-24.3%) suffered new pupillary asymmetry at any point during admission, 18% (95% CI: 12.6%-25.0%) suffered new motor deficit, and 22.4% (95% CI: 20.2-24.8) experienced death at 2 weeks.

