## DATA MANAGEMENT AND STATISTICAL ANALYSIS

All data including screening, inclusion/exclusion criteria, e-consent, randomization, and clinical data from all patients will be collected directly into a centralized electronic case report form supported by the MTBI^2^ Collection, Access, Sharing, and Analytics (CASA) platform system based in Henry Jackson Foundation Bethesda. National Institute of Neurological Disease and Stroke TBI-related common data elements from the following domains will be used: patient characteristics and history, disease/injury-related events, assessments and examinations, treatment/intervention data, protocol experience, and outcomes and end points (32) (Table 4).

**TABLE 4. T4:** Common Data Elements Collected: Domains, Measures, and Instruments

Domain	Subdomain	Measures/instruments
Participant characteristics and history	Demographics	Age, race/ethnicity, sex/gender, socioeconomic status, military service
	General health history	Significant medical history
Disease/injury Related events	Classification	Baseline risk assessment
		Injury severity score
		Head AIS
	History of disease/injury event	Injury presentation^a^
		Type, place, cause and mechanism of injury
	Discharge information	Discharge destination, time, and vital status
	Second insults	Aspiration, cardiac arrest, hyperventilation, hypotensive episode, seizure
		EEG monitoring
Assessments and examinations	Physical/neurological examination	Glasgow coma scale
		Pupil size, shape, and reactivity
		neurological pupil index
	Vital signs and other body measurements	Height and weight
		ICP monitoring
	Imaging	Cranial CT data
	Laboratory tests	Laboratory results (including INR and platelet count)
Treatment/intervention data	Surgeries and other procedures	ER/admission therapeutic procedures
		Surgical and therapeutic procedures
		Intraoperative management
	Therapies	Therapy intensity level
	Drugs	Prior and concomitant medications
Protocol experience	Participant/subject identification, eligibility, and enrollment	Informed consent
	Off treatment/off study	Study discontinuation/completion
Outcomes and end points	Disability	Glasgow outcome scale
	Adverse events	Severity: common terminology criteria for adverse events v6.0
		Expectedness: NIA adverse event and serious adverse event guidelines
		Causality: NIA adverse event and serious adverse event guidelines
		Neuroworsening events

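### The models for neuroworsening and death use age in groups although age itself is collected; one linear term would keep more information at no more cost in model terms.

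*Protocol article*

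**What the plan says.** All statements are in the protocol article.

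- **How age enters the models.** Outcomes, Primary Outcomes (analysis section): the multivariable models take the adverse outcomes as dependent variables, with "age group, sex, baseline ELD safety score, and pupillary abnormality as independent variables". The number of groups, the cut-points and a reason for grouping are not given.
- **How age is collected.** Table 4, demographics: "Age, race/ethnicity, sex/gender, socioeconomic status, military service". The element is age, not an age band. The inclusion criteria limit it to 18-65 years.
- **Selection of variables.** Same analysis section: "Logistic regression will be performed using those variables that have an association with outcome with a" P-value of .10 or less.
- **Other predictors.** The same paragraph plans univariate and multivariable analyses "using baseline variables, hourly NPI change, and volume of CSF drained per day for outcomes" (neuroworsening and death).
- **Arm comparison.** "Incidence of critical neuroworsening events will be compared between each arm, and between both ELD groups and control arm". No covariate is mentioned there, and the list of independent variables does not name treatment arm.
- **Size.** Randomization: "The study will enroll 30 severe TBI patients who will undergo 2-stage randomization".

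**The concern.** Grouping treats every patient within a band as the same age. If risk changes steadily with age, part of the covariate's information is lost, and with three or more bands the model uses more terms to carry less information. With 30 patients and few events, neither loss is easily spared.

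The P ≤ .10 rule adds to this. A weaker version of a covariate is less likely to pass, so grouping can decide whether age appears in the final model at all.

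Two kinds of result are exposed. The first is the prognostic models for neuroworsening and death. The second is any association reported for hourly NPI change or daily CSF volume: these are not randomized, so age can confound them systematically, and coarse adjustment leaves some of that confounding in place.

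**Working it through.** The article gives no figure on this point, so there is nothing to reproduce. The steps below size the loss.

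**Inputs from the article.** N = 30; age 18-65; selection at P ≤ .10; background rates from the registry analysis under Risks to Human Subjects: 22% ("suffered new pupillary asymmetry at any point during admission"), 18% new motor deficit, 22.4% death at 2 weeks.

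**Assumptions not in the article.** Age is either uniform on 18-65 or normal (mean 42, SD 14) truncated to 18-65. The age effect is linear on the logit scale, with an odds ratio of 1.3 to 2.0 per decade. Allocation is 10 control to 20 ELD (the ratio is not in the text, and the figure is not available). The event rate is 22%; the rate for the composite of Table 2 events may be higher.

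**1. Information kept by grouping.** This is the squared correlation of age with its grouped version. For a uniform variable in k equal bands it is 1 − 1/k². For a single cut with a fraction p below it, it is 3p(1 − p).

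| Grouping | Uniform | Truncated normal |
|---|---|---|
| 2 equal groups | 1 − 1/4 = 75% | 69% |
| 3 equal groups | 1 − 1/9 = 89% | 85% |
| 4 equal groups | 1 − 1/16 = 94% | 91% |
| Single cut at 30 | p = 12/47; 57% | 45% |
| Single cut at 55 | p = 37/47; 50% | 39% |

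The loss is 6-31% for two to four equal groups and 43-61% for the off-centre cuts.

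**2. Model terms against events.** Expected events of one type: 30 × 0.18 = 5.4; 30 × 0.22 = 6.6; 30 × 0.224 = 6.7. Count one term for each of the other three covariates, before interactions, NPI or CSF volume:

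- Linear age or two groups: 4 terms, 5.4/4 to 6.7/4 = 1.4 to 1.7 events per term.
- Three bands as categories: 5 terms, 1.1 to 1.3.
- Four bands as categories: 6 terms, 0.9 to 1.1.

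**3. Chance that age passes P ≤ .10.** 4000 simulated 30-patient trials per setting, 22% events, uniform age, Firth logistic regression with Wald tests:

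| Odds ratio per decade | Linear | Median split | Difference |
|---|---|---|---|
| 1.0 | 5.6% | 5.6% | 0 |
| 1.3 | 13.6% | 9.8% | 3.8 points |
| 1.6 | 27.7% | 20.4% | 7.3 points |
| 2.0 | 49.7% | 36.4% | 13.3 points |

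The first row shows that this test is conservative against a nominal 10%. With score tests and 30% events, the levels are higher but the order is the same: linear, median split and three bands pass in 46%, 39% and 33% of trials (odds ratio 1.6), and in 69%, 58% and 53% (odds ratio 2.0).

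**4. Effect on an age-adjusted arm comparison, if one were fitted.** The SD of age is 47/√12 = 13.57 years. With 10 against 20 patients, the chance difference in mean age has SD 13.57 × √(1/10 + 1/20) = 5.25 years. Shift in the treatment log-odds per 10 years of imbalance:

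| Odds ratio per decade | Unadjusted | Median split | Linear | Removed by split |
|---|---|---|---|---|
| 1.3 | 0.232 | 0.050 | −0.016 | 1 − 0.050/0.232 = 78% |
| 1.6 | 0.423 | 0.114 | −0.010 | 1 − 0.114/0.423 = 73% |
| 2.0 | 0.565 | 0.126 | −0.079 | 1 − 0.126/0.565 = 78% |

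At one SD of imbalance, the residual after a median split is 0.525 × 0.050 = 0.03 to 0.525 × 0.126 = 0.07 log-odds. Over these three settings the SD of the treatment estimate is 0.97-1.01 with the split and 0.97-1.08 with linear age.

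**The case against.** The strongest case for leaving the text alone has five parts.

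- **The arm comparison is hardly touched.** A reader might infer that grouping leaves age confounding in the safety comparison. The article does not support that. The arms are randomized, so only chance imbalance can remain. Incidence is compared directly, and the covariate list does not include treatment arm. Even in an adjusted comparison, a median split removes about three quarters of the imbalance. This part stands in full.
- **Grouping is not shown to be without benefit.** A linear term is better only if the logit is roughly linear in age, and in the simulation it did not reduce the SD of the treatment estimate. This stands: the advantage is conditional on linearity.
- **The screen may not use grouped age.** The article names age group only in the multivariable sentence, and the univariate analyses refer to baseline variables. The natural reading is still that the variables screened are those just listed, age group included. Linear age also fails the screen often, so recoding alone does not secure adjustment.
- **The sizes rest on assumptions.** Age distribution, allocation, odds ratios and event rate are assumed. The levels move with them; the direction does not as long as the age effect is near linear. The cost in extra terms needs more than two bands entered as categories, which the text does not say.
- **A condensed article leaves detail to other documents.** Number of groups and cut-points may well be set in a full protocol or SAP, and their absence is no finding. But grouping is itself stated, and no choice of cut-points recovers all of what it discards.

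**Conclusion.** The point holds as a minor efficiency matter. The article commits to grouped age where age itself is on the case report form and gives no reason. If the effect is roughly linear, the cost is 6-31% of the age information with two to four equal bands, more with an off-centre cut, and about 4 to 13 percentage points in the chance that a two-group age term passes the screen at odds ratios of 1.3 to 2.0 per decade and 22% events.

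The consequence lies in the prognostic models and in age adjustment for hourly NPI change and CSF volume. For the arms, the typical residual of 0.03-0.07 log-odds is negligible beside an SD near 1.0 and would not change the reading of the safety result. The P ≤ .10 screen and the number of model terms against 5-7 events of a type limit these models more than the coding of age does.

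**What to change.** In the Primary Outcomes analysis paragraph, replace age group with age in years, entered as a single linear term (for example per decade) in the univariate and multivariable models. Keep age bands for descriptive tables.

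The cost is one phrase. No new data are needed, and the change can be made before the data are released to the research team. It also removes any later choice of cut-points. The downside is the assumption that the log-odds change linearly over 18-65 years; if the investigators have a reason to doubt that, they should state it and fix the groups in advance. To make sure that age is adjusted for, it would also have to be exempt from the P ≤ .10 screen, which is a separate change.
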